## Abstract

**Introduction:** Innovative motor therapies have attempted to reduce upper extremity impairment after stroke but have not made substantial improvement as over 50% of people post-stroke continue to have sensorimotor deficits affecting their self-care and participation in daily activities. Intervention studies have focused on the role of increased dosing, however recent studies have indicated that timing of rehabilitation interventions may be as important as dosing and importantly, that dosing and timing interact in mediating effectiveness. This study is designed to empirically test dosing and timing.

**Methods and Analysis:** In this single-blinded, interventional study, subjects will be stratified on two dimensions, impairment level (Fugl-Meyer Upper Extremity Assessment (FM) and presence or absence of Motor Evoked Potentials (MEPs) as follows; (1) Severe, FM score 10–19, MEP+, (2) Severe, FM score 10–19, MEP–, (3) Moderate, FM score 20–49, MEP+, (4) Moderate, FM score 20–49, MEP–. Subjects not eligible for TMS will be assigned to either group 2 (if severe) or group 3 (if moderate). Stratified block randomization will then be used to achieve a balanced assignment. Early Robotic/VR Therapy (EVR) experimental group will receive in-patient usual care therapy plus an extra 10 h of intensive upper extremity therapy focusing on the hand using robotically facilitated rehabilitation interventions presented in virtual environments and initiated 5–30 days post-stroke. Delayed Robotic/VR Therapy (DVR) experimental group will receive the same intervention but initiated 30–60 days post-stroke. Dose-matched usual care group (DMUC) will receive an extra 10 h of usual care initiated 5–30 days post-stroke. Usual Care Group (UC) will receive the usual amount of physical/occupational therapy.

**Outcomes:** There are clinical, neurophysiological, and kinematic/kinetic measures, plus measures of daily arm use and quality of life. Primary outcome is the Action Research Arm Test (ARAT) measured at 4 months post-stroke.

**Discussion:** Outcome measures will be assessed to determine whether there is an early time period in which rehabilitation will be most effective, and whether there is a difference in the recapture of premorbid patterns of movement vs. the development of an efficient, but compensatory movement strategy.

**Ethical Considerations:** The IRBs of New Jersey Institute of Technology, Rutgers University, Northeastern University, and Kessler Foundation reviewed and approved all study protocols. Study was registered in https://ClinicalTrials.gov (NCT03569059) prior to recruitment. Dissemination will include submission to peer-reviewed journals and professional presentations.

## Introduction

Stroke is the leading cause of long-term adult disability (1). Independent upper extremity function is critically important to restore full independence and reduce the need for costly supportive care. Although innovative upper limb motor therapies, (2–5) have attempted to reduce upper extremity impairment after stroke, we have not made substantial improvement as over 50% of people post-stroke continue to have sensorimotor deficits that affect their self-care and ability to participate in daily activities (6). This lack of progress might be explained in part by the complexity of coordination of the multiple degrees of freedom required for normal upper limb function. Clearly, there is a need to develop more effective rehabilitation programs for the arm *and the hand* of persons with stroke.

The focus of recent rehabilitation studies has been on increasing the dosing and intensity of the interventions. Findings in a group of randomized controlled trials (7–10) indicated that the critical ingredients needed for arm and hand movement recovery may be the amount of treatment provided and the value of progressively increasing the level of difficulty of a task. The importance of dosage was further supported in a meta-analysis (11) of physical therapy interventions utilizing high repetition activities. These findings led to the growing consensus on the importance of intensity (number of repetitions per time on task) or dosage (time on task) to achieve better outcomes post-stroke. However, a recent phase 3 study of over 350 patients showed no differences among an additional 30 h of upper extremity structured task-oriented therapy, an equivalent dose of customary occupational therapy, or even a lower dose of customary therapy when these interventions were initiated 45 days post-stroke (12). Therefore, a consensus on optimal dosing in the early period post-stroke remains elusive (13).

It is apparent that it is not just dosing that needs to be considered. Several authors suggest that the timing of rehabilitation interventions may be as important as the dosing and have proposed that the dosing and timing of an intervention are not independent factors (14–16). Although the optimal time period is not clear, it has been shown that the first month post-stroke is a crucial time for synaptic plasticity where the brain is most responsive to sensorimotor input and training (14). The post-stroke sensitivity to intervention decreases as time post-stroke increases (17, 18). Both animal and human studies of early intervention reported better functional recovery [1–2 weeks in animals; 4 weeks in humans; (14, 19–21)] when training was initiated during the first month of recovery during this proposed period of intensive plasticity (14, 21–23). Thus, increasing rehabilitation treatment dose during this initial recovery period might have particularly beneficial effects. Nevertheless, most of the research on novel therapies involved subjects in the chronic phase after stroke, with a rather limited number of intervention studies available during the early and late acute phases (24).

However, contrary to these positive findings, some animal studies have shown that lesion size increased after early excessive limb training (25–27). Some human studies have also shown similar negative findings. Although, a meta-analysis of training studies showed a favorable effect on ADL resulted when augmented therapy was begun very early post-stroke (28), two studies did not find benefits from early intervention. The AVERT study was an early mobilization (<24 h) walking study and may not be an equivalent comparison (29). The Vectors study showed no differences between 2 h of early Constraint Induced Movement Therapy (CIMT) training and the control group but found less improvement with 3 h/day of early CIMT (30).

Therefore, it is particularly important to understand the impact of early motor training after stroke. Although, it has been proposed that early rehabilitation be integrated into comprehensive stroke centers to enhance care quality (31), the current state of health care delivery systems, in many countries, provides for limited in-patient rehabilitation post stroke. During this restricted time period, the focus is on ambulation and compensatory upper extremity activities necessary for activities of daily living. There is inadequate attention paid to rehabilitation and restoration of upper extremity movements so necessary for future independence in self-care activities. The conflicting evidence regarding timing, dosage and even the method of delivery of the increased dosing, robotics, virtual reality (32), or traditionally presented repetitive practice, suggests the need to examine both high volume training and method of training during the first-months post-stroke. Clearly, we do not yet have a good understanding of these relationships and their potential impact on recovery of motor function and brain reorganization.

### Study Aims and Hypotheses

This study is designed to empirically test the controversy regarding both the value of intensive, high dosage training as well as the optimal timing for intensive VR/Robotic training in the first 2 months after stroke. We are continuing an ongoing investigation into the effects of intensive task and impairment-based training of the hemiparetic upper limb with a focus on the hand using robotically facilitated rehabilitation interventions presented in virtual environments. The primary aim of this study is to test, at 4 months post-stroke, whether adding intensive VR/Robotic motor training to a patient's standard of care rehabilitation at 5–30 days post-stroke, improves functional outcomes of the hemiparetic hand when compared to initiating the additional VR/Robotic motor training 30–60 days post-stroke; thus testing the concept of optimal timing. Other comparisons include comparing Early VR to dose-matched usual care to test the potential benefits of the high-intensity VR/Robotic intervention. Comparing dose-matched usual care (10 additional hours of standard therapy) to usual care (no additional therapy) will inform about the benefits of increased dosing (Table 1). See controversies elucidated in recent literature (12, 30). We hypothesize that the outcomes will favor the early, high dosage VR/Robotic hand training group when compared to the delayed VR/Robotic training group and dose matched usual care group. The secondary aims will systematically investigate the mechanisms underlying the changes resulting from early timing of training and increased dosing, specifically changes in kinematics, kinetics, patterns of cortical somatotopic reorganization, and brain connectivity. We further hypothesize that the early, high dosage VR/Robotic hand training group will show a larger relative contribution of restored kinematic motor patterns to the overall improvement in motor function and these functional gains will be associated with the expansion of ipsilesional hand cortical somatotopy.

**Table 1 T1:** Comparison groups.

**Group comparisons**	**Intervention period^**+**^**	**Test**
EVR vs. DVR^*^	5–30 vs. 30–60 days	Timing of a VR/robotic intervention
EVR vs. DMUC^**^	5–30 days	VR/Robotic vs. conventional intervention
DMUC vs. UC^***^	5–30 days	Dosing of an intervention

* Early Virtual Reality vs. Delayed Virtual Reality,

** Dose Matched Usual Care,

*** *Usual Care; ^+^Time Post-Stroke*.

## Methods and Analyses

### Study Design and Setting

This is a single blinded, interventional study, with four randomized, parallel arms. Patients will be recruited at Kessler Rehabilitation centers in New Jersey. This study was approved by the Internal Review Boards of Kessler Foundation, Rutgers University, Northeastern University, and New Jersey Institute of Technology.

### Randomization and Recruitment

An independent statistician will generate the randomization sequence prior to initiation of the study. Physicians and therapists will identify potential subjects. The study coordinator will contact the patients as soon as they are medically stable, inform them about the study, screen them for inclusion and exclusion criteria and enroll them. The subjects will be stratified on two dimensions, impairment level and presence or absence of Motor Evoked Potentials (MEPs). Prior to randomization, potential subjects will be assessed using the Upper Extremity Fugl-Meyer Assessment (FM) (33) to establish motor impairment level, and Transcranial Magnetic Stimulation (TMS) for the presence or absence of MEPs in the lesioned hemisphere. These scores will be used to stratify subjects into four subgroups; (1) Severe, FM score 10–19, MEP+, (2) Severe, FM score 10–19, MEP–, (3) Moderate, FM score 20–49, MEP+, (4) Moderate, FM score 20–49, MEP-. If a subject is not eligible for TMS, he/she will be assigned to either group 2 (if severe) or group 3 (if moderate). This is based on the Stinear et al. (34) study in which study subjects with moderate impairment all had MEPs (34). Stratified block randomization will then be used to achieve a balanced assignment (35). For each of the four subgroups, every 4 subjects are one block. In each block, there is one subject for each type of treatment. One hundred twenty subjects will be assigned sequentially to four types of treatment groups (30 per group): (a) state-of-art usual care only (UC), (b) usual care plus an additional 10 h of usual care (dose-matched usual care, DMUC; initiated 5–30 days post-stroke), (c) usual care plus an additional 10 h of intensive therapy focusing on the hand using robotically facilitated rehabilitation interventions presented in virtual environments initiated **early** (5–30 days post-stroke) (EVR), and (d) usual care plus an additional 10 h of intensive therapy focusing on the hand using robotically facilitated rehabilitation interventions presented in virtual environments initiated later (30–60 days post stroke) (DVR) (see Figure 1).

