### Sample Size

For Aim 1, the planned primary analysis method is a mixed effect model. The primary outcome measure is the change in ARAT score from baseline evaluated at 4 months post-stroke. The estimated effect size for the interaction term is 0.42 (Cohen's f), and the estimated within-subject correlation is 0.7. For testing the hypothesis of Treatment Group (EVR, DVR, UC, DMUC) ^*^Test Time (Baseline, 4 M post-stroke, 6 M post-stroke) effect, and assuming compound symmetry correlation for within-subject measurements, for significance level 0.05, a total of 84 patients (21 for each group) are needed to detect the overall Treatment Group ^*^ Test Time interaction effect. But for the main planned contrasts, Treatment Group (EVR, DVR) ^*^ Test Time (Baseline, 4 M post-stroke) and Treatment Group (UC, DMUC) ^*^ Test Time (Baseline, 4 M post-stroke), a total of 96 patients (24 for each group) are required to detect the effect size of 0.42 between EVR and DVR or between UC and DMUC over time. Since detecting these contrasts is the main goal of the study, at least 96 subjects, 24 subjects per group, are required. After taking into account subject attrition, our total sample size will be equal to 120. We plan to run an interim analysis and update the sample size when we have recruited 50% of subjects.

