We will use the robust mixed effect model approach to analyze the data. We demonstrated in the past that this analytic approach is robust to detect treatment effects, even with relatively small groups of patients in whom within-group variance occurs with respect to stroke characteristics (56). Test Time (Pre, Post, 1-month post-treatment, 4 months post-stroke, 6 months post-stroke) and Treatment Group (EVR, DVR, DMUC, UC) will be treated as fixed effects in the mixed models. The interaction term between Test Time and Treatment Group will be included. Baseline measurements will be added as a covariate into mixed models for outcome variables. Random intercept will be used to model subject-level variation. Covariance pattern and model selection will be implemented with likelihood-based tests. Contrasts to compare group means will be applied to obtain comparisons between time, and between treatments, with multiplicity adjustment considered. We have an a priori interest in specific Test Time by Treatment Group interaction effects for the EVR-DVR, for the DMUC-UC, and for the EVR-DMUC comparisons. The particular differences we are interested in are Pre vs. Post and Pre vs. second (4 months post stroke) retention assessments. In the case of balanced data and equal variances, we will use the Tukey procedure to test for significant interaction effects, otherwise, Bonferroni correction will be used. In our design, the timing comparison is the difference between EVR and DVR. The dosage comparison is the difference between UC (usual care) and the DMUC (usual care plus 10 additional hours). In addition, we will be able to compare the type of training effect, VR vs. dose-matched usual care (EVR vs. DMUC), where both types of training are delivered in the same time period.

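### Randomisation is blocked within FM-severity by MEP strata, but the mixed model has no stratum term, so the treatment contrasts may be reported with too large a standard error

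*Protocol article*

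**What the plan says.** Under Randomization and Recruitment, the article forms four strata from Fugl-Meyer (FM) severity (10–19 or 20–49) and the presence or absence of MEPs: "The subjects will be stratified on two dimensions, impairment level and presence or absence of Motor Evoked Potentials (MEPs". Blocks of four are used within each stratum: "In each block, there is one subject for each type of treatment". Patients who cannot have TMS are placed by severity: "If a subject is not eligible for TMS, he/she will be assigned to either group 2 (if severe) or group 3 (if moderate".

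Under Statistical Analysis, the mixed model has fixed effects for test time and treatment group. "The interaction term between Test Time and Treatment Group will be included". The baseline measurement is a covariate and a random intercept represents the subject. The comparisons of interest are group-by-time contrasts, including Pre versus 4 months post-stroke. Neither that section nor Sample Size names a stratum, FM-severity or MEP term. Management of Statistical Assumptions discusses covariates in general and does not mention the stratification factors.

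**The concern.** Blocking within strata makes the arms alike on severity and MEP status. Chance imbalance on these factors then contributes almost nothing to the true variability of an arm difference. A model without the strata does not know this: it leaves any between-stratum variance in the error term and reports a standard error that includes it. Confidence intervals come out too wide and p-values too large.

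What is at stake is power and calibration. The sample size has little slack, because 24 per arm is the smallest number that gives 80% power at the planned effect size (80% is assumed; the article states no power). The plan also corrects for multiplicity by Tukey or Bonferroni. If the sample-size update at 50% recruitment uses the model's residual variance, the overstatement would carry into it.

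**Working it through.** **Inputs from the article (Sample Size).** "The estimated effect size for the interaction term is 0.42 (Cohen's f), and the estimated within-subject correlation is 0.7"; "for significance level 0.05, a total of 84 patients (21 for each group) are needed" for the overall interaction; "a total of 96 patients (24 for each group) are required to detect the effect size of 0.42 between EVR and DVR"; "After taking into account subject attrition, our total sample size will be equal to 120".

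**Assumed, because not stated.** Power 80%; attrition 20%; and R², the share of 4-month ARAT variance left after baseline that the strata explain, taken as 0.05–0.20.

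**1. The plan's own figures.** Noncentral F with λ = f²N and f = 0.42:
- Two groups, df 1 and 2n − 2: n = 23 gives power 0.796 and n = 24 gives 0.813, so 24 per group reproduces.
- Overall interaction, df 6 and 2(N − 4): N = 80 gives 0.797 and N = 84 gives 0.821, so 84 reproduces.
- 96 / (1 − 0.20) = 120.

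No stratum term enters any of these.

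**2. Type I error without the strata.** With strata balanced by blocking, the true variance of the arm difference is (1 − R²) times the variance the model reports. Normal approximation: type I error = 2[1 − Φ(1.96/√(1 − R²))].

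| R² | 1.96/√(1 − R²) | Type I error |
|---|---|---|
| 0.05 | 2.011 | 0.044 |
| 0.10 | 2.066 | 0.039 |
| 0.20 | 2.191 | 0.028 |

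**3. Power at 24 per arm.** For two equal groups d = 2f = 0.84.
- Without strata: 1 − Φ[(c·s − d)/(s√(1 − R²))], with s = √(2/24) = 0.289 and c = 2.013 (t, 46 df). At R² = 0.10 this is 1 − Φ[(0.581 − 0.84)/0.274] = 0.828.
- With strata: noncentral F with λ = (d²n/2)/(1 − R²), df 1 and 43.

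| R² | Without strata | With strata | Loss (points) |
|---|---|---|---|
| 0.05 | 0.821 | 0.831 | 1.0 |
| 0.10 | 0.828 | 0.850 | 2.3 |
| 0.20 | 0.842 | 0.889 | 4.7 |

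**4. Which term repairs the planned contrast.** Simulation: 400 trials per setting, four equal strata, 24 per group, within-subject correlation 0.7, random-intercept model with Pre kept as a level of test time. Here R² is the share of the variance of change due to the strata. Standard error of the group-by-time Pre versus 4-month contrast:

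| R² | No strata | Stratum main effect | Stratum × test time | Empirical SD |
|---|---|---|---|---|
| 0.10 | 0.2315 | 0.2315 | 0.2229 | 0.2212 |
| 0.20 | 0.2411 | 0.2411 | 0.2227 | 0.2218 |

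The main effect does nothing, because a term constant over time cancels from a change. The interaction brings the reported standard error close to the empirical one. The variance ratios are (0.2315/0.2229)² = 1.08 and (0.2411/0.2227)² = 1.17. The implied type I errors, 2[1 − Φ(1.96 × ratio of standard errors)], are about 0.042 and 0.034, inside the range in step 2.

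**5. The alternative model.** For post-baseline ARAT with baseline ARAT as covariate, a stratum main effect is enough: the standard error falls from 0.220 to 0.202 (R² = 0.10) and from 0.235 to 0.201 (R² = 0.20), with an empirical SD of about 0.20 throughout. These reductions are larger than 1 − R² implies, because the simulated strata also carry severity that baseline captures imperfectly. They show direction and mechanism, and the size is better read from steps 2 and 3.

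**The case against.** **The article may not list every term.** It never says that its list is exhaustive. It mentions likelihood-based model selection and collinearity checks among covariates, and a statistical analysis plan that is not shown could contain the strata. It is fair that nothing excludes them. But the model is written out term by term, and further fixed effects are named where wanted in the kinematic and neurophysiological analyses. Neither model selection nor a collinearity check prespecifies a stratum term.

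**The predictive value is undocumented.** A reader might infer that the strata were chosen because they predict recovery, and that MEP status predicts ARAT beyond baseline. The article gives only balanced assignment as the purpose of stratified blocking. Its Discussion calls neurophysiological measures promising biomarkers with few studies behind them. It also cites a study in which all moderately impaired patients had MEPs, so the moderate/MEP-negative stratum may be nearly empty. Baseline ARAT probably absorbs part of severity, and placing TMS-ineligible patients by severity blurs MEP status. This stands: the size is an assumption and could be close to zero.

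**The loss is easily overstated.** Since 24 × (1 − R²) is 21.6 at R² = 0.10 and 19.2 at R² = 0.20, a reader might infer that 24 per arm act like 19–22. That confuses reported with true precision, because blocking has already delivered the balance. An adjusted analysis would need about 22.6 and 21 per arm to match the unadjusted power at those two values. Unadjusted power stays at 0.82–0.84, not below the 0.813 that reproduces the plan's 24. This objection also stands.

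**Conclusion.** The point holds as a matter of efficiency and calibration. Randomisation is blocked within four strata and the stated model ignores them. For an assumed R² of 0.05–0.20, type I error is about 0.044–0.028 instead of 0.05, and about 1–5 points of power are lost at 24 per arm. Both figures depend on that assumed R², for which the documents give no value; if the strata add nothing beyond baseline ARAT, the effect is negligible.

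A reader might infer that the primary test is invalid. It is not: omitting balanced strata neither biases the estimate nor inflates type I error, and the test errs on the cautious side. The weight is minor to moderate.

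**What to change.** Add the randomisation stratum, as randomised, and its interaction with test time to the primary ARAT model. Use the four levels, or FM severity and MEP status as separate main factors (each crossed with test time) if the moderate/MEP-negative cell is nearly empty. An equivalent route is to model post-baseline ARAT with baseline ARAT and the strata as covariates.

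Keep TMS-ineligible patients in the stratum in which they were randomised. A separate not-testable MEP level departs from the strata used for blocking and belongs, if wanted, in an optional sensitivity analysis.

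Both factors are recorded before randomisation, so no new data are needed. The cost is a short addition to the model description and about 3 degrees of freedom per time point.

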### Data Collection and Management

The assessment schedule is summarized in Table 2. Pre-post training assessments will take place at the KIR. The 1-month post therapy, 4 and 6-month post-stroke assessments will take place either at KIR, NJIT, or at Rutgers University. The clinical tests for all subjects will be assessed by an evaluator blinded to group assignment (see Table 2). Study data will be maintained in locked files and password protected computers. The code containing subject ID's will be maintained by the study coordinator.

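### The fixed, published block of four (one patient per arm) would let enrolling staff who can follow earlier assignments deduce up to a quarter of allocations; mixed, undisclosed block sizes would cut this cheaply

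*Protocol article*

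**What the plan says.** All of the following is in the protocol article.

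- **Block rule** (Randomization and Recruitment): "For each of the four subgroups, every 4 subjects are one block" and "In each block, there is one subject for each type of treatment". No variation in block size is mentioned.
- **Strata** (same section): "The subjects will be stratified on two dimensions, impairment level and presence or absence of Motor Evoked Potentials (MEPs"), which gives four strata.
- **Timing of the stratum assessment** (same section): "Prior to randomization, potential subjects will be assessed using the Upper Extremity Fugl-Meyer Assessment (FM"), together with TMS for MEP status.
- **Size** (same section): "One hundred twenty subjects will be assigned sequentially to four types of treatment groups (30 per group").
- **Who makes the list** (same section): "An independent statistician will generate the randomization sequence prior to initiation of the study".
- **Who enrols** (same section): "The study coordinator will contact the patients as soon as they are medically stable, inform them about the study, screen them for inclusion". The rest of that sentence gives the coordinator the check of exclusions and the enrolment itself.
- **Blinding** (Study Design and Setting; Measures; Data Collection and Management): the trial is called single blinded, and the only person described as blinded is the clinical assessor.
- **Coordinator's other tasks**: keeping the code with subject IDs (Data Collection and Management), and checking participant files and data entry (Ethical Consideration).

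**The concern.** With a known block of four and one patient per arm, the fourth place follows by elimination once three arms have appeared. Generation of the list by an independent statistician hides the list but does not prevent this deduction. It needs only the block rule, which is published, and knowledge of past assignments in the stratum. Past assignments are hard to hide here: the arms are early robot/VR sessions, delayed robot/VR sessions, ten extra hours of usual care, or nothing extra.

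Following four short sequences is also easy at the expected pace of 25–30 patients a year (Current Results).

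Someone who knows the next arm can influence who is enrolled, and when. Some eligibility judgements leave room for that, such as whether a patient is well enough to train, or whether aphasia or neglect would prevent the tasks. The EVR–DVR, EVR–DMUC and DMUC–UC contrasts all rely on comparable arms. The authors also state a directional hypothesis in favour of EVR and are testing a system that their own group developed. Blinded assessment does not correct selection at entry. Adjustment for baseline does not remove selection on unmeasured prognosis.

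**Working it through.** **The plan's own figure.** 120 patients / 4 per block = 30 blocks. One patient per arm in each block gives 30 per group, as stated, if every block is completed.

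**Allocations known with certainty, fixed blocks of 4.** Over all 24 orderings of a block, only the last place is determined by the earlier ones, so the share is 1/4 = 25%.
- All blocks complete: 30 of 120 = 25%.
- Unfinished blocks: each of four strata can end with up to 3 patients in an open block, at most 12 in all. Then (120 − 12)/4 = 27 complete blocks, and 27/120 = 22.5%.
- In the third place of each block (another 25%), only two arms remain possible.
- By symmetry, half of the certain places are EVR or DVR: about 15 of 30.

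**Best-guess hit rate, fixed blocks of 4.** The chance of a correct guess at places 1 to 4 is 1/4, 1/3, 1/2 and 1. The mean is (1/4 + 1/3 + 1/2 + 1)/4 = 25/48 = 52.1%. Simple randomisation gives 25%.

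**Blocks of 4 and 8 in random order.** Assumptions: the two sizes are equally likely, each stratum has 30 patients, and the guesser knows both sizes but not their order and guesses optimally. In 4,000 simulated sequences, 6.4% of allocations were certain and the hit rate was 47.1%.

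The like-for-like values for fixed blocks with 30 patients in a stratum (7 complete blocks and 2 patients over) are:
- certain: 7/30 = 23.3%;
- hit rate: (7 × 25/12 + 1/4 + 1/3)/30 = 15.17/30 = 50.6%.

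So certainty falls by a factor of almost four, while the hit rate moves by only a few points.

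**Cost in balance.** The article gives no stratum sizes, so three splits of 120 were assumed. The measure is the mean largest difference between arm totals, by simulation.

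| Assumed strata | Fixed 4 | Mixed 4/8 | Increase |
|---|---|---|---|
| 35/20/60/5 | 1.50 | 2.11 | 0.61 |
| 33/19/58/10 | 2.19 | 2.51 | 0.32 |
| 30/30/30/30 | 2.34 | 2.59 | 0.25 |

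**Cost in power.** The Sample Size section uses Cohen's f = 0.42 and 24 per group. For two groups, d = 2f = 0.84. A plain two-sample t test at the 0.05 level, used only to gauge sensitivity to imbalance, has 81.3% power with 24/24 and 81.2% with 23/25.

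**The case against.** A reader might infer that a quarter of allocations are in fact fully predictable to the coordinator. The article does not support that. Deduction needs two things that it does not state.

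1. **Knowledge of earlier assignments in the stratum.** The coordinator's access to assignments is not described. The code with subject IDs might be read as an allocation record, but it is mentioned beside locked files and password protection, and reads as a confidentiality key. The file-checking role and the visible treatments make knowledge of past assignments likely, but this is inference.
2. **Knowledge of the next patient's stratum before the decision to enrol.** Fugl-Meyer is an eligibility criterion, so it is known at screening. MEP status needs TMS. The article places it before randomisation and speaks of potential subjects, but does not say who sees the result or whether it precedes the decision to enrol. Without it, the enroller would be choosing between two lists. For moderate patients that is little protection, because the article cites a study in which all such patients had MEPs.

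A reader might also call the trial open-label. That is not the article's term: it says single blinded. What stands is that treatment is visible to those who deliver it, and that assessor blinding does not protect allocation.

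Other limits on exploitation are real. Physicians and therapists identify candidates, several criteria are scored, and the start window for two arms limits how long a patient can be held back. A DSMB watches adherence to eligibility. Stratification and the baseline covariate limit bias from measured severity. These reduce the risk but do not remove it.

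Finally, four is the smallest block that balances four arms, and it is a defensible choice with four strata, one of which (moderate, MEP–) may be very small. Nothing in the plan is contradictory or miscalculated. The method of concealment may be in the full protocol, and its absence from an article is no fault. Concealment of the list alone would not stop deduction at the end of a block.

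**Conclusion.** The point holds as a conditional risk. The article fixes and publishes a block of four with one patient per arm in each stratum. If enrolling staff can follow assignments and know the stratum in advance, 27 to 30 of 120 allocations could be deduced with certainty, and the best-guess hit rate would be 52% against 25% by chance. A quarter is the maximum, reached only when all blocks are complete. Nothing in the article shows that anyone used such knowledge or that bias occurred. The change below is an inexpensive improvement, not the correction of an error. Its main gain is the removal of most certain predictions; overall guessability falls only modestly.

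**What to change.** Have the independent statistician regenerate the part of each stratum's list that has not yet been used, with block sizes of 4 and 8 in random order. Withhold the sizes from everyone who screens or enrols. Keep the four strata, the 1:1:1:1 ratio, the sample size and the analysis.

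The cost is a new list for patients not yet randomised and slightly looser balance, as tabulated above, with power almost unchanged. The article reports seven patients with completed six-month tests but not the number randomised, so how much of the list is still unused must be checked first. The benefit applies only to that part.
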